##### Acceptability: quantitative

Percentage of responses observed in “yes” to the following item—“Would you be willing to wear the belt again as a part of a new research study?” will be calculated at wave *W*, where *W* = W1 or W2 or W3. The lower bound threshold is < 75%. The upper bound threshold is ≥ 85%.

##### Acceptability: qualitative

Themes that emerge from responses to the five qualitative items designed to assess acceptability will be analyzed at wave *W*, where *W* = W1 or W2 or W3. Possible improvements will be considered with regard to the protocol for accelerometer-based assessment of free-living physical activity within the FFW online intervention among adults with obesity in the USA. Specifically, improvements will be considered with regard to instructions for wearing the belt, acceptability of wearing of the belt, remembering to wear the belt, integration of wearing the belt into the daily routine, and why some participants may be unwilling to wear the belt as a part of new research study. The lower bound threshold is the presence of at least one potentially serious problem with the accelerometer-based protocol that is unable to be addressed in a future study. The upper bound threshold is the absence of a potentially serious problem with the accelerometer-based protocol that is unable to be addressed in a future study.

#### Aim 4

Inferential statistical models under both an intent to treat (ITT) approach and a complier average causal effect (CACE) approach will be used to provide a preliminary effect size estimate for each direct effect depicted in the conceptual model (see Fig. 2) for the FFW online intervention (e.g., FFW → Physical Activity) at wave W, where W = W2 or W3. Using both an ITT approach and a CACE approach is consistent with data analyses from the 2015 FFW efficacy trial [36, 38, 39] and with the data analysis plan for the 2018 FFW effectiveness trial [37]. Covariates, the outcome at W1, and group assignment will be specified as predictors in both approaches. Threshold values for the traffic light system for the specific indicators that will be used to evaluate aim 4 are based on commonly used heuristics for Cohen’s *d* [76].

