#### Acceptability

The acceptability of accelerometer-based assessment of physical activity will be assessed with a modified version of a questionnaire used in previous research [46, 61]. The 11-item acceptability questionnaire used in this study consists of a mix of both Likert-scale quantitative (6) and open-ended qualitative (5) items. The first item assesses relevant previous experience “Have you ever wore a physical activity monitor (e.g., Fitbit) to measure physical activity prior to enrolling in this study?”, ___ no, ___ yes. The next eight items are matched pairs where a quantitative item is paired with a qualitative item to assess a particular aspect of acceptability (i.e., instructions, acceptability of wearing the belt, remembering to wear the belt, integration into daily routine). For example, the second item is “the instructions included in the physical activity monitoring package were easy to follow”, 1 = strongly disagree, 2 = disagree, 3 = neutral, 4 = agree, 5 = strongly agree. Whereas the third item is “If you selected disagree or strongly disagree for the previous item, will you please tell us why the instructions were difficult to follow?”. The penultimate item is “Would you be willing to wear the belt again as a part of a new research study?”, 0 = no, 1 = maybe, 2 = yes. The final item is “What, if anything, would you suggest that we change about how the belt is to be worn in this research study?”

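### Aim 3 means to consider why some participants would not wear the belt again, but no item in the acceptability questionnaire asks them why

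*Protocol article*

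**What the plan says.** The questionnaire is set out under Data collection, Acceptability: "The 11-item acceptability questionnaire used in this study consists of a mix of both Likert-scale quantitative (6) and open-ended qualitative (5) items". The items are then described in order.

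- Item 1: "The first item assesses relevant previous experience", answered no or yes.
- Items 2 to 9: "The next eight items are matched pairs where a quantitative item is paired with a qualitative item". The four topics are "instructions, acceptability of wearing the belt, remembering to wear the belt, integration into daily routine".
- Item 10: whether the participant would wear the belt again in a new study, coded no, maybe or yes.
- Item 11: "What, if anything, would you suggest that we change about how the belt is to be worn in this research study".

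One paired open item is given as an example: "If you selected disagree or strongly disagree for the previous item, will you please tell us why the instructions were difficult to follow". The wording of the other three is not shown.

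Under Data analysis, Aim 3, Acceptability: qualitative, themes from the five open items are to be analyzed at each wave, and improvements considered on five topics. The fifth is "why some participants may be unwilling to wear the belt as a part of new research study". Acceptability: quantitative scores item 10 by the percentage answering yes: red below 75%, green at 85% or more.

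**The concern.** A topic that the plan undertakes to consider should have a question that brings in answers on it. Four of the five Aim 3 topics do. For the fifth, a participant who answers no or maybe on willingness is not asked the reason. The next and last item asks for suggestions about how the belt is worn, and a reason for declining need not take that form: the mailing, the daily log, the repeated monitoring weeks or plain lack of interest may never be mentioned.

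Aim 3 asks how to implement accelerometry in a later trial. A willingness percentage short of green says that something needs attention but not what. Reasons that were not asked for at a wave are hard to recover afterwards.

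**Working it through.** **Item count.** Inputs are from Data collection, Acceptability.

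- Quantitative: item 1 + four paired items + item 10 = 1 + 4 + 1 = 6.
- Open: four paired items + item 11 = 4 + 1 = 5.
- Total: 6 + 5 = 11.

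This reproduces the stated 11 items and the stated split of 6 and 5. There is no room for an open item that the article leaves undescribed.

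**Topics against items.** The five topics are from Aim 3, Acceptability: qualitative.

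| Aim 3 topic | Open item that asks about it |
|---|---|
| Instructions | Paired open item |
| Acceptability of wearing | Paired open item |
| Remembering | Paired open item |
| Daily routine | Paired open item |
| Reasons for unwillingness in a new study | None; item 10 is closed, and item 11 asks for changes to how the belt is worn |

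So 4 of 5 topics have their own open item and 1 of 5 has none.

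**How many people this could concern.** Inputs are the target of 30 (Sample size) and the 75% and 85% thresholds (Acceptability: quantitative; Table 2). Assume that all 30 answer item 10 at a wave.

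- 0.75 × 30 = 22.5 and 0.85 × 30 = 25.5.
- Green: at least 26 yes, so at most 30 − 26 = 4 not yes.
- Yellow: 23 to 25 yes, so 5 to 7 not yes.
- Red: at most 22 yes, so at least 30 − 22 = 8 not yes.

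In the yellow and red ranges, 5 to 7 or at least 8 participants would have answered no or maybe without being asked directly for the reason. With fewer respondents the counts shrink, but the missing question is the same.

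**After the change.** One open item after item 10 gives 6 quantitative + 6 open = 12 items, and all five topics then have a matching open item.

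**The case against.** The strongest reply is that the reasons are not lost. Item 11 has no condition, follows directly on the willingness item, and gives anyone who has just answered no or maybe a place to say what was wrong. The paired items cover wearing and daily routine, which are obvious reasons for refusing. The Data analysis section names comments from the center's staff as a further example of qualitative material, and the Recruitment section explains that the local setting was chosen so that staff can follow up with participants. Aim 3 also promises only to consider improvements on the topic, not to analyze it separately. All of this stands, and it limits the point to reasons being captured indirectly.

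Three stronger readings are tempting, and the document does not support them.

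- A reader might infer that the open items reach only those who disagree. The condition "If you selected disagree or strongly disagree for the previous item" is shown for one of the four paired items, as an example; for the other three it would be an inference, and item 11 goes to everyone.
- A reader might infer that the planned analysis has no data at all. Item 11 and the paired items can both bring out relevant reasons.
- A reader might infer that the qualitative traffic light is tilted toward green. This is not shown. One serious problem that cannot be addressed is enough for red, the assessment is made at three waves, and unwillingness is scored separately by the willingness percentage, where a maybe counts against green.

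The Discussion concedes that open-ended questions may miss information that interviews would find. That is a general caution; it does not say that one named topic has no question, and interviews are not needed to supply one.

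**Conclusion.** The mismatch is real but minor. The questionnaire gives four of the five Aim 3 topics their own open item; reasons for unwillingness have none and can be learned only indirectly. It would matter mainly if the willingness indicator came out yellow (5 to 7 of 30 not answering yes) or red (8 or more), because Aim 3 would then have little direct information on why. Those counts are illustrations that assume full response at a wave; the article does not predict where the indicator will fall. No effect estimate or other feasibility rate is affected. The conclusion rests on the article's item list being complete, which its own count supports.

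**What to change.** Add one open item directly after the willingness question, for example: *If you selected no or maybe, please tell us why.* The questionnaire becomes 12 items, six quantitative and six open. Update the count under Data collection, Acceptability, and change five qualitative items to six under Aim 3, Acceptability: qualitative, so that the two sections agree.

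The cost is one extra short item at each wave, shown only to those who answer no or maybe, and a minor ethics amendment. Rewording item 11 to ask for the reason would keep the total at 11, but would give up or blur the request for suggested changes, so the added item is preferable.

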### Sample size

Thirty participants will be targeted for enrollment in this study. There are three rationales for the target sample size. First, the target sample size fits well within the range of sample sizes often observed in pilot and feasibility trials [45]. Second, and with regard to aim 1 through aim 3 of this study, the target sample size is consistent with sample sizes observed in similar research [31, 46–48]. Third, and with regard to Aim 4 of this study, the target sample size is based on budgetary constraints and not a sample size determination for a desired level of statistical power [42–44]. Budgetary constraints preclude enrollment of more than 30 participants in this study.

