### Randomization

Following completion of the W1 survey battery, participants will be randomly assigned to either the FFW group or the usual care (i.e., UC) group by the code programmed within the FFW website that is specified to achieve a 1:1 group (i.e., *n*_FFW_ = 15_,_
*n*_UC_ = 15) assignment.

Participants, center staff, and research staff will be blinded to participant group assignment.

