#### W1, W2, and W3 survey battery

Instruments designed to measure demographic information, anthropometric characteristics, self-efficacy, and well-being will be included in the survey battery. Data on proposed demographic covariates of well-being [63] and/or physical activity [9] will be collected in the W1 survey battery and will include participant gender, age, race, education-level, marital status, and annual income. Residential zip code data will be collected in the W1 survey battery as a proxy for a host of built environment factors that may be related to an individual’s level of physical activity [9]. Anthropometric data will be assessed in the W1 through the W3 survey battery by asking each participant their height and weight. Demographic, zip code, and anthropometric variables are collectively referred to as covariates from this point forward.

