### Data analysis

Data analyses will include both quantitative and qualitative approaches. Quantitative analyses will be performed in M*plus* 8.0 under maximum-likelihood estimation with robust standard errors [72]. Missing data will be handled with the default approach under the assumption that data are missing at random [73]. When an estimate of a population parameter (e.g., mean difference) is sought, estimation of a 95% confidence interval (CI) will also be sought. When a qualitative approach is taken (e.g., responses to an open-ended acceptability item; feedback from the center staff), feedback will be summarized based on themes that emerge from the research team’s analysis of the feedback. The particular quantitative and/or qualitative methods that will be used to evaluate each specific aim will vary as a function of the focus of the specific aim.

A traffic light system will be used to evaluate results of specific indicators within each specific aim and with regard to the feasibility of a future definitive RCT [43]. Data observed below a lower threshold (i.e., red light) will indicate a potentially serious problem. Data observed above a lower threshold but below an upper threshold (i.e., yellow light) will indicate that caution is warranted. Data observed above an upper threshold (i.e., green light) will indicate support for the feasibility of a future definitive RCT. The particular threshold values that define the traffic light system will vary by the specific indicator within each specific aim (see Table 2).

**Table 2 Tab2:** Lower and upper bound threshold values that define the traffic light system by aim

Aim	Lower bound threshold	Upper bound threshold
Aim 1		
Acceptability	< 60%	≥ 80%
Recruitment rate	< 40%	≥ 60%
Eligibility rate	< 60%	≥ 80%
Consent rate	< 80%	≥ 90%
Participation rates	< 50%	≥ 70%
Retention rates	< 40%	≥ 60%
Aim 2		
Pearson’s correlation	< .60	≥ .70
Bland-Altman analyses	> 10% of observations beyond M ± 2SD	≤ 5% of observations beyond M ± 2SD
Aim 3		
Acceptability: Quantitative	< 75%	≥ 85%
Acceptability: Qualitative	At least one potentially serious problem	Absence of a potentially serious problem
Aim 4		
Intent to treat	< 0.00	≥ 0.20
Complier average causal effect	< 0.00	≥ 0.20
Indirect effects	Not available	Not available

#### Aim 1

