##### ITT

The ITT approach will estimate each direct effect of being assigned to the FFW intervention at wave *W*, where *W* can equal W2 or W3 [77]. The lower bound threshold is < 0.00. The upper bound threshold is ≥ 0.20.

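### Aim 4 fits at least 11 predictors to at most 30 people with robust ML, so its 95% ITT intervals probably under-cover; separately, its light ignores the interval

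*Protocol article*

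**What the plan says.** **Model.** The Aim 4 text under Data analysis says "Covariates, the outcome at W1, and group assignment will be specified as predictors in both approaches", meaning ITT and CACE. The survey battery section defines the term: "Demographic, zip code, and anthropometric variables are collectively referred to as covariates from this point forward". The demographic variables are gender, age, race, education level, marital status and annual income; zip code is added; the anthropometric variables are height and weight. On timing it says "Anthropometric data will be assessed in the W1 through the W3 survey battery", and the definition of covariates names no wave.

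**Size.** Under Sample size: "Budgetary constraints preclude enrollment of more than 30 participants in this study". For Aim 4, "the target sample size is based on budgetary constraints and not a sample size determination for a desired level of statistical power". Allocation is 1:1, 15 per group.

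**Estimation.** Data analysis specifies Mplus maximum likelihood with robust standard errors and seeks a 95% confidence interval for each estimated population parameter. It does not say how the interval is formed.

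**Light.** The ITT and CACE sections both say "The lower bound threshold is < 0.00. The upper bound threshold is ≥ 0.20", on the Cohen's d scale. Data analysis applies the lights to the observed value: below the lower threshold signals a potentially serious problem, above the upper one supports a definitive RCT, and between them (here 0.00 to below 0.20) is yellow. The interval has no role.

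**The concern.** There are two separate faults.

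1. **Interval.** Robust (sandwich) standard errors are a large-sample device. With 12 coefficients, including the intercept, and 30 people or fewer, the fitted residuals are much smaller than the true errors. The standard error is then too small, and a 1.96 multiplier makes no allowance for the few residual degrees of freedom. An interval labelled 95% would suggest far more certainty about the preliminary effect size than the data hold.

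2. **Light.** The red and green cut-offs are 0.20 apart, while the standard error of d is 0.30 or more in the base case below. A light read from the point estimate is then mostly noise, yet it is to be read as evidence on the feasibility of the definitive RCT.

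**Working it through.** The plan gives no standard error, power or coverage figure for Aim 4, so there is none of its own to reproduce.

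**Inputs from the protocol article**
- Predictors: 6 demographic + 1 zip code + 2 anthropometric = 9; plus W1 outcome and group = 11; with the intercept p = 12. One column per variable is the lenient count.
- n = 30 at most.
- Accelerometer MVPA: unusable data are treated as missing. The green threshold for participation (70%) gives 0.70 × 30 = 21; that for retention (60%) gives 0.60 × 30 = 18.
- Cut-offs for d: 0.00 and 0.20.

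**Assumptions not in the article**
- Interval = estimate ± 1.96 robust SE.
- Normal data with SD 1 and a true effect of zero.
- W1-to-follow-up correlation ρ = 0.6 (range 0 to 0.8).
- The nine covariates are unrelated to the outcome. This affects the precision comparison, not coverage.

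**Step 1: coverage, approximate formula.** ML divides the residual sum of squares by n instead of n − p, so the SE shrinks by √((n − p)/n). With ordinary ML errors, coverage = P(|t with n − p df| < 1.96 × √((n − p)/n)).
- n=30: 1.96 × √(18/30) = 1.518; 18 df; 85.4%.
- n=21: 1.96 × √(9/21) = 1.283; 9 df; 76.8%.
- n=18: 1.96 × √(6/18) = 1.132; 6 df; 69.9%.

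The robust version is slightly worse. Simulation (4,000 to 12,000 data sets per cell) gives:

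| n | 11 predictors, robust ± 1.96 | 11 predictors, t-based | group + W1 outcome only, robust ± 1.96 |
|---|---|---|---|
| 30 | 83–84% | about 95% | 92–93% |
| 21 | 74–75% | about 95% | 90% |
| 18 | 66–67% | about 95% | 90% |

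Coverage hardly depends on ρ (83–84% at n=30 over 0 to 0.8). If multi-category covariates raise the count to 15 or 18 columns, coverage at n=30 falls to 78% or 72%.

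**Step 2: standard error of d.** With q predictors besides group, SE² ≈ (1 − ρ²) × (4/n) × (1 + q/(n − q − 3)). At ρ = 0.6 the first factor is 0.64.
- q=10, n=30: 0.64 × 0.1333 × (1 + 10/17) = 0.1355; SE 0.37.
- q=10, n=21: 0.64 × 0.1905 × (1 + 10/8) = 0.2743; SE 0.52.
- q=10, n=18: 0.64 × 0.2222 × (1 + 10/5) = 0.4267; SE 0.65.
- q=1 (W1 outcome only): SE 0.30, 0.36 and 0.39 at the same n.

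**Step 3: ITT light when the true d is zero.** P(red) = P(d < 0) = 50% by symmetry. P(green) = 1 − Φ(0.20/SE):

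| n | 11 predictors | group + W1 outcome only |
|---|---|---|
| 30 | 1 − Φ(0.20/0.368) = 29% | 1 − Φ(0.20/0.298) = 25% |
| 21 | 1 − Φ(0.20/0.524) = 35% | 1 − Φ(0.20/0.359) = 29% |
| 18 | 1 − Φ(0.20/0.653) = 38% | 1 − Φ(0.20/0.390) = 30% |

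Simulation agrees within about two points (29–31% at n=30 for the planned model). Over ρ from 0 to 0.8 the planned model gives 23–34% at n=30 and 32–40% at n=18. An unadjusted comparison at n=30 gives 29%.

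**Not assessed.** All coverage figures are for ITT; none was computed for CACE.

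**The case against.** The strongest reply is that Aim 4 is openly preliminary and unpowered, that Aims 1–3 are the purpose of the study, and that no rule turns an Aim 4 light into a go/no-go decision or a sample size. That is correct and limits the consequences. It excuses wide intervals, but not intervals that carry a 95% label and under-cover, nor a red or green call on the future RCT that ignores the interval.

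A second reply is consistency with the earlier FFW analyses, which the article cites. That is a real benefit, but the 2018 trial enrolled about 900 people, and what large-sample errors tolerate at that size does not carry over to 30.

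Several stronger readings are tempting, and the article does not support them:
- **That the long covariate list causes the false green lights.** At n=30 it moves them from about 25% to 29–31%. Small n and the point-estimate rule do most of the work.
- **That 67% applies to all of Aim 4.** The counts 21 and 18 concern usable accelerometer data only. No attrition figure is given for the questionnaires; with complete data the figure is 84%.
- **That CACE intervals fail to the same degree.** This was not tested.
- **That W2 or W3 weight will be adjusted for.** The text collects weight at every wave and does not restrict the covariate to W1, but states no such adjustment.
- **That zip code must be a meaningless slope or one level per person.** It is described as a proxy for the built environment and could be linked to an area measure.
- **That a definite number of lights will be produced.** This depends on a figure not shown and on how the scales are scored.

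**Conclusion.** The concern holds in two separate parts.

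**Interval.** With at least 11 predictors, at most 30 people and robust ML, a nominal 95% ITT interval covers about 84% with complete data. For accelerometer MVPA it covers about 75% to 67% at the plan's own green thresholds for usable data. This rests on the interval being estimate ± 1.96 robust SE, which the article does not state, and on normal data. It does not depend materially on the W1 correlation.

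**Light.** With a true effect of zero, the ITT light is red about half the time and green about 25–38% of the time. The lower end is the W1-outcome-only model at n=30, the upper end the planned model at n=18, both at an assumed correlation of 0.6. Over correlations 0 to 0.8 the planned model gives about 23–40%. The yellow zone does not rescue this, since it takes only the remainder. Trimming the model therefore repairs most of the interval problem but not the light, which needs its own change.

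**What to change.** 1. Remove the ITT and CACE rows from the Table 2 traffic light. Report d with its 95% interval as descriptive, and state that it will not decide on the definitive RCT.
2. Limit the ITT model to group and the W1 outcome, plus at most one or two baseline covariates named in advance. State that any anthropometric covariate is the W1 value.
3. Use a small-sample t-based interval for ITT. Label the CACE interval approximate, or form it with a small-sample method such as the bootstrap.

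Item 3 restores about 95% ITT coverage in the simulations. Item 2 lowers the SE of d from 0.37 to 0.30 at n=30 and from 0.65 to 0.39 at n=18, if the dropped covariates are unrelated to the outcome; the gain is smaller if they are prognostic. Only item 1 deals with the misleading lights.

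Cost: rewording the Aim 4 text and two table rows, with no added participants, visits or data. The downside is less demographic adjustment, less consistency with the earlier FFW analyses, and no light for Aim 4.

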### Data collection

#### Study timeline

Three waves of data will be collected over a 13-week period (see Fig. 3), which is similar to both the 2015 FFW efficacy trial [36] and the 2018 FFW effectiveness trial [37]. Data collection at W1 will include the W1 survey battery and W1 physical activity monitoring. The W1 survey battery will be completed in week 1. The W1 physical activity monitoring will be completed in week 2. Participants will return physical activity monitoring items (to be detailed in the physical activity monitoring section) to the research staff in week 3. The intervention will be delivered in week 3 through week 6. Data collection at W2 will include the W2 survey battery and W2 physical activity monitoring. The W2 survey battery will be completed in week 7. The W2 physical activity monitoring will be completed in week 8. Participants will return physical activity monitoring items to the research staff in week 9. Data collection at W3 will include the W3 survey battery and W3 physical activity monitoring. The W3 survey battery will be completed in week 11. The W3 physical activity monitoring will be completed in week 12. Participants will return physical activity monitoring items to the research staff in week 13. The timeline for this study is similar to timelines used in other physical activity interventions in adults with obesity [6, 32, 33].

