#### ActiGraph wGT3X-BT

The ActiGraph wGT3X-BT (Pensacola, FL, USA) is a tri-axial research-grade accelerometer that will be used to measure physical activity objectively. ActiGraph devices have been used extensively as a reference (e.g., gold-standard) device to measure free-living physical activity objectively in adults [29]. Monitors will be initialized to collect raw acceleration data at 30 Hz using ActiLife software (version 6.13.3). Upon download, data will be re-integrated to 60-s epochs, and non-wear time will be defined as ≥ 90 continuous minutes of zero counts, with allowance for 2 min of acceleration that are preceded and followed by at least 30 min of continuous zeros [59]. Usable data will be defined as follows: (a) a log sheet with a valid start date is submitted, (b) a monitor is worn for at least 4 days (including one weekend day) with at least 10 h of valid wear time per day, and (c) no evidence of monitor error (e.g., activity counts > 20,000 or lengthy strings of repeated activity counts). Unusable data will be treated as missing data. Average minutes per day of MVPA will be calculated based on established cut points (e.g., > 1952 counts per minute) [60].

The cost of an ActiGraph wGT3X-BT is approximately 225 USA dollars. The ActiGraph wGT3X-BT can store data up to 43 days and sync wirelessly with the ActiLife mobile application; however, the wireless function will be disabled to maximize battery life. A participant will not be able to view any physical activity displays while wearing this device. The pairing of the ActiGraph wGT3X-BT with the Fitbit Zip is based on previous research where at least a moderately high correlation and a moderate level of agreement between measures of average minutes per day of MVPA produced by these two accelerometers has been observed [47, 48].

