##### Retention rates

Retention rate through wave *W*, where *W* = W2 or W3, will be defined as the percentage of consented patients who provide usable data at W1 through wave *W*: (*n*_usable data through wave W_/*n*_consent_) × 100. The lower bound threshold is < 40%. The upper bound threshold is ≥ 60%. The definition of usable data will follow the description previously provided in the *ActiGraph wGT3X-BT* section.

#### Aim 2

Pearson’s correlation coefficient and Bland-Altman analyses will be used to determine if accelerometer-based assessment of physical activity *should* be used within the FFW intervention. Threshold values for the traffic light system for the specific indicators that will be used to evaluate aim 2 are based on inferences drawn from the results of previous research [47, 48].

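### As most naturally read, Aim 4 estimates the W3 effect without the W2 outcome, so W3 missingness that depends on W2 differently by arm can bias it

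*Protocol article*

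**What the plan says.** Under Data analysis, Aim 4, the protocol article seeks a preliminary effect size for each direct effect "at wave W, where W = W2 or W3", under both ITT and CACE. The model content is fixed in one sentence: "Covariates, the outcome at W1, and group assignment will be specified as predictors in both approaches". The ITT paragraph repeats the indexing: "The ITT approach will estimate each direct effect of being assigned to the FFW intervention at wave" W2 or W3. The traffic light is red below 0.00 and green from 0.20 on the Cohen's d scale.

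The opening of Data analysis names the estimator, "maximum-likelihood estimation with robust standard errors" in Mplus, and the missing-data rule: "Missing data will be handled with the default approach under the assumption that data are missing at random". For accelerometry, "Unusable data will be treated as missing data".

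The timeline puts W2 well before W3: "The W2 physical activity monitoring will be completed in week 8", and W3 monitoring follows in week 12. No joint model of W2 and W3 is named, and no auxiliary variable.

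**The concern.** Missing at random is always relative to what the model contains. In a model with W3 as the only outcome and the W1 outcome, covariates and group as predictors, it means that W3 missingness is unrelated to the W3 outcome once those predictors are known. A participant whose progress at W2 influences whether usable W3 data arrive falls outside that condition, although the W2 value that would bring the case back inside is in the database.

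The article contains routes by which this could happen and could differ by arm:

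- Participants with usable data are sent their average MVPA within a few weeks of returning the monitors. W2 monitors come back in week 9, so some may see their W2 result before W3 monitoring in week 12.
- W2 payment is $10 in usual care. In FFW it is $25, tied to at least 30 completed challenges.
- Poor wear counts as missing, as well as dropout.

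At stake is the W3 light and the preliminary effect size carried into planning a definitive trial. A confidence interval shows sampling error but would not show this bias.

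**Working it through.** **No planned figure to reproduce.** The sample size for Aim 4 is set by budget, and the article gives no SD, correlation or expected missingness for these models. The only check is the split, 30/2 = 15 per arm.

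**Why a W3-only likelihood ignores W2.** Write X for the W1 outcome and covariates, and G for group.

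- Separate model: each observed participant contributes f(Y3 | X, G). A participant with Y3 missing contributes the integral of that density over Y3, which is 1. Maximum likelihood therefore equals a complete-case regression at W3.
- Joint model: the contribution is f(Y2 | X, G) × f(Y3 | Y2, X, G). A participant with Y2 but not Y3 still contributes the first factor. The W3 group effect is γ_G + γ_2 × α_G, where α_G is the group effect on Y2, and γ_G and γ_2 are the coefficients of group and Y2 in the model for Y3. This is the total effect of assignment at W3, the same quantity the separate model targets.

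**Inputs from the article.** 15 per arm; green from 0.20; red below 0.00; W3 participation green from 70%; retention through W3 green from 60%.

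**Inputs assumed.** W1, W2 and W3 normal with unit variance and equal correlation 0.5 or 0.7; W3 retention 40% to 80%; W3 missingness logistic in the W2 outcome with slope 1 or 2 per SD; true effect 0, 0.2 or 0.5 SD; W2 observed for everyone.

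**Bias of the W3 effect, large-sample simulation:**

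| Dependence of W3 missingness on W2 | W3 retention | Separate W3 model | Joint W2 and W3 model |
|---|---|---|---|
| Same in both arms, no effect | 40–80% | about 0 | about 0 |
| Same in both arms, d = 0.2 | 40–80% | −0.005 to −0.02 | about 0 |
| Same in both arms, d = 0.5 | 40–80% | −0.01 to −0.06 | about 0 |
| FFW only, slope 1 | 80% | +0.04 to +0.05 | about 0 |
| FFW only, slope 1 | 60% | +0.07 to +0.09 | about 0 |
| Opposite directions by arm, slope 1 | 80% | +0.08 to +0.09 | about 0 |
| Opposite directions by arm, slope 1 | 60% | +0.15 to +0.17 | about 0 |

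The joint model stayed within about 0.006 SD of the truth throughout. The arm-specific rows are positive because FFW participants with low W2 values are the ones lost. Reversing the pattern reverses the sign.

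**At 15 per arm** (true d = 0.2, correlation 0.7, 60% retention, FFW-only dependence, slope 1):

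- Mean estimate 0.267 separate and 0.197 joint; the difference is 0.070.
- SD of the estimate 0.361 separate and 0.356 joint.
- Chance of green 0.56 separate and 0.49 joint.

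**A harsher setting** (no true effect, n = 30, wave correlations 0.7/0.7/0.6, 41% missing at W3, FFW-only dependence on the W2 residual with slope 1.0 to 1.5):

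- Bias +0.10 to +0.14 separate and 0.00 joint.
- Green in 41% to 44% of runs separate and 30% joint.
- A rerun with a different scaling of the residual reached +0.18 at slope 1.5, so steeper slopes can exceed the table.
- Under completely random missingness the joint SD was 0.39 against 0.41, so joint fitting costs no precision here.

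**The case against.** The strongest reply is that the article never says the waves are fitted separately. A list of predictors is equally true of a model with W2 and W3 as two outcomes, and the wave index is used throughout the article as shorthand. A reader might infer that the plan discards W2 on purpose; the text does not say so. If W2 is already a second outcome in the likelihood, the concern disappears. Joint or wave-wise fitting is also detail that a full analysis plan often supplies. This stands as a limit on certainty. It does not remove the point: predictors, estimator and missing-data rule are all given, one model per wave is their plain reading, and a better model is available from the same data.

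Three stronger readings are tempting and not supported.

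- **That any W2-dependent dropout biases the effect.** It does not. With the same relation in both arms the bias is nil at no effect and small otherwise.
- **That FFW participants who saw no gain are expected to leave.** The article gives routes for this but no evidence. W3 payment is $10 for the same tasks in both arms, and the usable-data rule is not arm-specific.
- **That up to 40% may be missing at W3 while the light stays green.** Retention through W3 requires usable data at every wave, so some of that 40% may be missing at W1 or W2. The W3-only figure is participation, green from 70%, so at most 30% missing. Both rates concern accelerometry; no missingness figure is given for the survey scales.

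It is also fair that Aim 4 is labelled preliminary and that sampling error exceeds the bias. Joint fitting does not make the light reliable: in the harsher setting it still shows green 30% of the time with no effect.

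**Conclusion.** The point holds as a conditional one. If each wave is fitted alone, as the text most naturally reads, the W3 effect is open to bias from W3 missingness that depends on W2 differently by arm. The size is about +0.04 to +0.17 SD for a slope of 1 per SD, correlations of 0.5 to 0.7 and 60% to 80% W3 retention, against a yellow band of 0.20 − 0.00 = 0.20. With equal dependence in both arms it is near zero at no effect and at most about 0.06 SD, toward zero, at d = 0.5.

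The correlations, slopes and dropout patterns are assumptions, since the article gives none, and the simulations assume W2 is observed for all. The CACE model was not simulated. The change is worth making because it uses data already collected and costs no precision in the settings tried. It is a modest improvement to a pilot estimate whose sampling error is larger than the bias.

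**What to change.** For the ITT analysis, state that W2 and W3 of each outcome are fitted together: both as dependent variables, with the same predictors (covariates, W1 outcome, group) and correlated residuals. A repeated-measures model with arm by wave would serve equally. Read the W2 and W3 group effects from that model.

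Do not add W2 as an ordinary predictor of W3. It is measured after randomisation, and conditioning on it would change the effect being estimated.

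In the CACE model, do the same only if it estimates stably with 15 per arm. If it does not, keep the wave-wise model and say that its W3 effect relies on missingness being unrelated to W2 given W1, covariates and arm.

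For ITT the cost is model syntax in the software already named, plus a few extra variance parameters at n = 30, which favours a short covariate list. Participants who lack W2 data as well as W3 data gain nothing from the change.
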